### The baseline quantitative survey

#### Data collection

Two separate questionnaires were developed in English and then translated into Bangla for the girl’s and community surveys. The Bangla version of the questionnaires were pre-tested and cognitive interviews were conducted during 10–14 December 2018 in two villages from Rangpur district, which were outside the TPI study area. Scales not used previously in Bangladesh and questions deemed difficult to comprehend were identified for cognitive interview. Both the Bangla and English versions of the questionnaires were then modified based on the feedback received from the pre-test. The questionnaires were finalized after piloting conducted at the end of the survey team training.

A team of 14 females and two males with graduate degree collected the baseline data. The team was accompanied by four supervisors, two quality control officers and one survey coordinator. The survey team received a 12-day participatory training from 8–29 January 2019 on gender, child marriage, empowerment of women and adolescent girls, survey methods, the questionnaire, research ethics, use of tablets, data collection techniques, field management, and data quality.

The baseline survey was conducted from 2 February – 9 April 2019 using separate pre-designed questionnaires for adolescent girls and community members. Data were collected face-to-face in Bangla by gender-matched interviewers upon receipt of oral assent of adolescent girls and oral consent of their parents in the girls’ survey and oral consent of the participants in the community survey. All the interviews took place in private, in a location convenient for the participants, and used tablets. The survey coordinator was responsible for coordinating survey implementation in the field. The supervisors assigned daily tasks to the interviewers and received feedback at the end of each working day. A selected participant was considered unavailable if the survey team could not reach her/him after three visits during the whole period of data collection.

#### Data quality monitoring

A comprehensive data quality monitoring system was in place. At the first level, the supervisors observed and spot-checked the interviews and provided feedback to the interviewers, if there was any. The researchers made frequent field visits, randomly checked filled-out questionnaires, observed interviews where possible and provided feedback to the survey team. Secondly, the quality control officer checked each completed questionnaire for any inconsistencies and solved the issue in consultation with the interviewers. Further, a computer-based data checking routine was developed and inconsistencies of collected data were checked routinely. Problems identified in the data were communicated to the supervisors through the survey coordinator. The supervisor resolved the problems through discussion with the interviewer if possible. If necessary, the interviewer revisited the respondent and solved the issues by consulting the respondent. Moreover, 5% of the interviews were revisited by the supervisor and they administered a short questionnaire focused mainly on identifying any problems in adhering to ethical guidelines and administering questions on particular topics.

#### Scale construction and reliability checks

In preparation for endline data collection and analysis, the study team validated the scales using the baseline data and the number of items in the scales was reduced using factor analysis. The rotated factor loading of an item against all the suggested factors was checked for non-loading and cross-loading. The cut-off for item loading was set at 0.35. An item was considered as cross-loaded if it loaded under two or more factors. The analysis was rerun excluding the non-loaded and cross-loaded items one by one. This process continued until no non-loaded or cross-loaded item was left. Any factor with less than three items was dropped. Internal consistency (or reliability) of a scale was measured using Cronbach’s alpha. A scale with alpha equal to 0.60 or more was considered acceptable. Scale validity was measured using the Kaiser–Meyer–Olkin (KMO) test. KMO equal to 0.60 or more was considered acceptable.

#### Baseline survey data analysis

The household enumeration data were used to estimate the baseline proportion of child marriage among males (married before age 21) and females (married before age 15, and 18). Using the baseline survey data, the basic background characteristics (e.g. age, education, religion, and ethnic group) of the girl and community samples were compared by arm (control, TPP, and TPP+) to check the arm balance. The arms were considered balanced if there were no or few significant differences in background characteristics.

Descriptive analyses were carried out using the baseline data to report mean score, proportion, tertiles of score for selected outcomes. All group differences were assessed using χ^2^-tests of independence for categorical variables and t-tests for continuous variables. Significance level was set at p < .05 for all bi-variate analyses. The baseline analyses were conducted in STATA 15.

### The endline quantitative study

The same cohort of adolescent girls and separate cross-sectional samples of adult male and female community members were interviewed during the endline, ten months after the end of intervention. The questionnaires were updated to include specific questions on exposure and participation on TPI, exposure and impact of COVID on outcomes. Additionally, items are dropped from scales based on scale validation performed on baseline data. An approach similar to baseline is being followed in interviewing the study participants.

#### Impact evaluation analysis

Intention-to-treat analysis will be used for assessing the impact of the TP program. Thus, all the TP girls enrolled in TPI will be included in the analysis irrespective of their actual level of participation in the intervention activities. The impact of the TP program on primary outcome, child marriage will be assed using hazard ratio while the TP secondary outcomes will be assessed using risk ratios derived from binary regression analyses for measuring change in outcomes in the intervention arms relative to change in the control arm. Mixed-effects models will be constructed with clusters as random effects and time point, intervention group, and time point x intervention interaction as fixed effects. Adjusting for the dependent variables at baseline survey we will obtain a measure of the relative change in intervention group that took place between baseline and endline compared to the change in the control group. The background characteristics for which the differences between study arms are evident, the pre-existing differences will be controlled in subsequent analyses. All analyses will be adjusted for the potential factors associated with the outcomes of interest.

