#### Recruitment of study participants and formation of groups

From the household enumeration data, a list of eligible girls and community members was prepared. Girls were eligible for the study if they were: i) aged 12-<16 years; ii) unmarried; and currently living in the study village. Adult males and females aged 25 or more and currently living in the study village were considered eligible to participate in the community survey.

Simple random samples of 29 eligible girls were drawn from each cluster. We oversampled the girls by 16% to achieve a group size of 25, considering the possibility of refusal. In addition, six eligible adult males and six eligible adult females were selected at random from each village for the community survey. In intervention clusters, the lists of selected girls were provided to the implementing organization, which then approached girls from the list of 29 in random order to invite them to participate in the TPI until they had enrolled the 25 target participants per cluster. These girls were then approached to participate in the study, specifically the baseline survey, by the research team. In control villages, and for the adult community samples in each cluster, the research team directly invited the randomly selected participants to enrol in the study during the baseline survey, administered the consent form and interviewed the individuals.

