### Challenges and limitations

First of all, collecting accurate information on age is always a challenge in countries like Bangladesh where most people do not usually keep track of age, and birth registration is a recent phenomenon. To deal with this issue, we provided intensive training to the household enumerators and data collectors on several strategies to determine age as accurately as possible. For example, recalling any historical events related to the birth like flood, draught, political event, etc. In case of girls, age at menarche was used as an additional check. In these circumstances, it is likely that the participants in household enumeration were not always able to provide correct information on age. Thus, some of the randomly selected eligible respondents from enumeration data were found ineligible when they were screened for their age at the time of the survey. We have replaced these cases with eligible girls. The survey team cross-checked the reported age with the birth registration card, but sometimes such cards were not available.

Secondly, reporting of age at marriage may be biased also in an attempt to avoid disclosing illegal CM. We tried to minimize this bias by calculating the birth year, marriage year and duration of marriage. Thirdly, in intervention clusters the girls who agreed to participate in the program were recruited and interviewed. This may result in possible selection bias. To avoid this bias, in control communities we added a hypothetical question on their willingness to participate in such program. Only three girls mentioned that they would not participate in such program. Thus, it can be said that the girls are not different from those in the intervention communities and minimizes the possibilities of selection bias.

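### Girls entered the cohort only after accepting the programme in the two intervention arms but not in control, so the planned analysis is not intention-to-treat of the girls drawn, and a hypothetical question does not show that the groups are alike

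*Protocol article*

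**What the plan says.** *Impact evaluation analysis* states: "Intention-to-treat analysis will be used for assessing the impact of the TP program". It then spells out the set: "all the TP girls enrolled in TPI will be included in the analysis irrespective of their actual level of participation in the intervention activities".

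*Recruitment of study participants and formation of groups* describes how girls came into that set. The starting point was the same in every village: "Simple random samples of 29 eligible girls were drawn from each cluster". In intervention villages the implementing organization "approached girls from the list of 29 in random order to invite them to participate in the TPI until they had enrolled the 25" it was aiming for, and then: "These girls were then approached to participate in the study, specifically the baseline survey, by the research team". In control villages the research team invited the drawn girls to the survey itself, with no programme offer in between.

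*Household enumeration* places enumeration, and so recruitment, after randomization. *Blinding* says that nobody was blinded.

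*Challenges and limitations* acknowledges that "in intervention clusters the girls who agreed to participate in the program were recruited and interviewed" and that this may cause selection bias. As mitigation it reports a hypothetical willingness question put to control girls, to which three answered no. It concludes: "Thus, it can be said that the girls are not different from those in the intervention communities", and that the possibility of selection bias is thereby reduced.

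**The concern.** Randomization balances the villages and, through a random draw within each village, the girls drawn. It does not balance subsets formed after allocation by a step that exists in some arms only. Accepting a programme of weekly sessions is such a step. Girls whose families declined were never surveyed in the TPP and TPP+ villages. Their counterparts in control villages stayed in the cohort if they consented to a survey.

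The first two study objectives, the effect of TPP and of TPP+ on child marriage, rest on the two comparisons with control. If girls who decline differ in marriage risk, those comparisons show a difference even when the programme does nothing. Readers who see an intention-to-treat label and a statement that the groups do not differ would have no reason to allow for it.

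The planned adjustment does not settle this for the primary outcome. All girls were unmarried at entry, so adjusting for the baseline value of the outcome removes nothing. Adjusting for background characteristics acts only on measured traits among girls who enrolled.

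**Working it through.** **Entry routes side by side**

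| Step | TPP and TPP+ villages | Control villages |
|---|---|---|
| Random draw | 29 eligible girls | 29 eligible girls |
| Who approaches first | Implementing organization | Research team |
| First request | Join the programme | Join the survey |
| Next request | Survey, for programme enrollees only | None |
| Analysed | Programme enrollees, whatever their attendance | Survey enrollees |

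The programme-acceptance step is present in two columns of the trial and absent from the third, and it follows allocation.

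**The plan's own figures**

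- Oversampling: 25 × 1.16 = 29, as stated.
- Sample size: 50% against 35% (reading the 15% effect as percentage points), two-sided 5%, 80% power, with continuity correction, gives 182.4 girls per arm. The design effect is 1 + 21 × 0.05 = 2.05. Then 182.4 × 2.05 / 22 = 17.0 clusters per arm, and 51 × 25 = 1,275. The stated size reproduces; the point concerns who is analysed.

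**The hypothetical question**

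Three unwilling girls out of a planned 17 × 25 = 425 in control is 0.7% (exact 95% interval 0.1% to 2.1%, ignoring clustering and assuming that all 425 answered). This is stated willingness in control. It measures neither actual refusal in the intervention villages nor how the refusers differ.

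**How large the bias could be**

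The documents give neither the refusal rate nor the refusers' risk, so both are assumed. Let *p* = 0.50 be the risk among all girls drawn (the protocol's planning value), *r* the proportion refusing and *k* the refusers' risk relative to acceptors. With no programme effect, the acceptors' risk *x* solves (1 − *r*)*x* + *rkx* = *p*, so *x* = *p* / (1 + *r*(*k* − 1)). The spurious difference is *p* − *x*, if control loses nobody for the same reasons.

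| Refusal *r* | *k* = 1.5 | *k* = 2 |
|---|---|---|
| 0.7% (control girls' stated unwillingness) | 0.50 − 0.498 = 0.2 points | 0.50 − 0.496 = 0.4 points |
| 5% | 0.50 − 0.488 = 1.2 points | 0.50 − 0.476 = 2.4 points |
| 14% (upper bound, 4/29) | 0.50 − 0.467 = 3.3 points | 0.50 − 0.439 = 6.1 points |

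The 14% row is the most that a list of 29 can lose and still yield 25. Its *k* = 2 cell implies a refuser risk of 2 × 0.439 = 88%, which is extreme.

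**Effect on the test.** At *r* = 4/29 and a refuser risk of 80%, *x* = (0.50 − 0.138 × 0.80) / 0.862 = 0.452, a difference of 4.8 points. With an effective 17 × 22 / 2.05 = 182 girls per arm, the two-sided type I error rises from 5% to about 15%. At *r* = 5% and the same refuser risk it is about 6%.

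**Reversed sign.** If refusers have a 30% risk at *r* = 4/29, *x* = (0.50 − 0.138 × 0.30) / 0.862 = 0.532, and the spurious difference is −3.2 points, against the programme.

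**The case against.** The strongest defence has five parts.

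- **The approach was in random order.** This limits the implementer's discretion, and where the first 25 girls accepted, four were never approached at all. That stands: a reader might infer that the implementer hand-picked girls, and the text does not support it. Random order does not remove the girls' own choice to decline.
- **4/29 is not a refusal rate.** It is a contingency applied in every cluster, control included. That stands. A reader might take about 14% as what happened; it is only a ceiling, and the one willingness figure in the article gives a bias of a few tenths of a point.
- **The direction is not known.** It is tempting to say that families who decline a girls' rights programme marry daughters earlier, so the bias flatters the programme. The article also reports that many girls were busy most of the day with school and tutoring. If such girls declined, and have lower risk, the bias runs the other way.
- **Control girls also needed assent and parental consent.** Some reluctant families would drop out there too, so only the net difference matters. That stands, and it makes the figures above upper-end illustrations for each assumption.
- **The objectives refer to girls participating in the programme.** The set matches that wording in the intervention arms. The control group, however, is then not restricted to girls who would have accepted, so the comparison remains unlike with unlike.

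The article also discloses the risk and does not say that bias is excluded outright. Its replacement of age-ineligible girls is not described as differing by arm, so it is no evidence of differential selection.

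**Conclusion.** The point holds as a matter of design and labelling. Cohort entry was conditional on programme acceptance in both intervention arms and not in control, after unblinded allocation. The set described in *Impact evaluation analysis* is therefore not intention-to-treat of the randomly drawn girls, and the conclusion in *Challenges and limitations* that the girls do not differ does not follow from the evidence given.

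The size is uncertain. Under an assumed 50% risk it runs from about 0.2–0.4 points, through 1.2–2.4, to 3.3–6.1 at the upper bound, and to about −3 points if refusers have lower risk. For fixed *r* and *k* it shrinks in proportion if the true risk is below 50%. The documents do not support a claim that the bias is large or that it favours the programme. TPP+ against TPP is less exposed because both arms recruited in the same way, although acceptance could still differ between them.

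**What to change.** 1. In *Impact evaluation analysis*, describe the set as girls who enrolled, analysed by village allocation, and state that this is not intention-to-treat of the girls drawn.
2. Add a sensitivity analysis that weights the enrolled girls in each arm back to that arm's drawn list, using enumeration variables such as age, education and religion. State that it corrects measured traits only and cannot reach family attitudes.
3. Add a second sensitivity analysis that excludes the three unwilling control girls, so that control is closer to programme-willing girls. Expect little change from so few.
4. Report by arm the numbers approached, declined and replaced, where the implementing organization recorded them. The article does not say that refusals were logged; if they were not, say so.
5. In *Challenges and limitations*, replace the conclusion that the girls do not differ with a statement that selection bias in the comparisons with control cannot be excluded.

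The cost is wording plus analysis of enumeration data already collected, with slightly wider intervals in the weighted analysis. Recruitment is over, so nothing here restores the girls who declined.

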***CM – Child marriage**

**KMO – Kaiser-Meyer-Olkin test**

### Quantitative surveys

The quantitative component includes baseline and endline (10 months after the end of intervention) data collection from the same cohort of adolescent girls and separate cross-sectional samples of adult male and female community members in all 51 study villages.

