#### Sample size

The sample size for the quantitative component was calculated based on the primary outcome ‘child marriage’ among girls aged between 12 years and below 16. The rate of CM for this age group was unknown. Thus, we assumed a 50% prevalence rate and considered a cluster size of 22 adolescent girls. A life skills intervention in Maharashtra, achieved 19% reduction in CM in the community [38]. Based on this, we assumed a 15% effect size and an Intra-Cluster Correlation of 0.05. Considering 5% significance level and 80% power we required 17 clusters per arm making the total number of clusters 51. Considering a 15% non-response/dropout rate the group size increased to 25 and total sample size increased to 1,275 girls. To assess social norms change we considered child marriage related social norms among the adult community members aged 25 or more as the primary outcome. Since the prevalence of CM related norms is unknown in the study villages, we assumed it to be 50%. Considering a 15% effect size, 5% significance level, 80% power and 5% non-response rate, we required 540 community members from 51 clusters. To ensure participation of both males and females we required six adult males and six adult females from each cluster.

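### For the secondary outcomes, the two-wave model with only a village random intercept does not fit the girls' or the adults' data, and the text also describes a second, different estimator

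*Protocol article*

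**What the plan says.** The section Impact evaluation analysis of the protocol article divides the outcomes by effect measure: "child marriage will be assed using hazard ratio while the TP secondary outcomes will be assessed using risk ratios derived from binary regression analyses". It then gives one model specification: "Mixed-effects models will be constructed with clusters as random effects and time point, intervention group, and time point x intervention interaction as fixed effects". The next sentence says: "Adjusting for the dependent variables at baseline survey we will obtain a measure of the relative change in intervention group". No other random effect is named.

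The section Quantitative surveys describes two data structures, with data taken from the "same cohort of adolescent girls and separate cross-sectional samples of adult male and female community members". The section on the endline quantitative study repeats this. Girls are therefore a closed cohort measured twice, and adults are fresh samples at each round.

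On entry to the cohort: "Girls were eligible for the study if they were: i) aged 12-<16 years; ii) unmarried; and currently living in the study village". Child marriage therefore has no baseline measurement.

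**The concern.** Two things do not fit together.

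1. **The random effects do not match the data.** A village intercept that is the same at both rounds cancels out of a before-after contrast. Unless all villages in an arm drift in step, the time-by-arm term is left with almost no allowance for clustering, although villages were randomised. For girls, the model also treats one girl's two answers as independent given her village.

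2. **Two estimators are described as one.** A model with baseline rows as outcomes and a time-by-arm term estimates a difference of changes. Adjusting endline for baseline is a different estimator with a different variance. For adults no individual baseline value exists.

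At stake are the confidence intervals and p-values of the secondary outcomes. These include the adult norms outcome, for which the Sample size section sizes a separate survey at 80% power.

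**Working it through.** **The plan's own figure first.** Inputs from Sample size: 50% prevalence, a 15-point effect (50% v 35%), ICC 0.05, 22 girls per cluster, 5% significance (taken as two-sided), 80% power.
- Design effect: 1 + 21 × 0.05 = 2.05.
- With continuity correction: 183 × 2.05 / 22 = 17.05 clusters per arm. Without: 170 × 2.05 / 22 = 15.84, or 16.84 with one cluster added.
- The stated 17 reproduces. It rests on a single endline comparison, so the analysis model does not affect it.
- Adults: 3 × 170 / 0.95 = 537, against the stated 540.

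**Notation.** k = 17 villages per arm, m people per village per round, ρ = 0.05, total variance 1. CAC is the correlation of a village's effect between rounds. IAC is the within-girl correlation given the village (0 for adults). The document gives neither CAC nor IAC, so both are assumed. The ICC of 0.05 is stated for the girls' calculation, so using it for adult outcomes is also an assumption.

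**Standard error of the time-by-arm term (linear scale)**
- True variance = (4/k) × T, where T = ρ(1−CAC) + (1−ρ)(1−IAC)/m.
- Model variance with a village intercept only = (4/k) × s²/m, where s² ≈ [2(m−1)(1−ρ) + mρ(1−CAC) + (1−ρ)(1−IAC)] / (2m−1).
- SE ratio (model/true) = √[(s²/m)/T]. True type I error = 2 × [1 − Φ(1.96 × ratio)].

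| Group | m | CAC | IAC | T | s²/m | SE ratio | Type I error |
|---|---|---|---|---|---|---|---|
| Adults | 11 | 1.0 | 0 | 0.0864 | 0.0864 | 1.00 | 5.0% |
| Adults | 11 | 0.8 | 0 | 0.0964 | 0.0868 | 0.95 | 6.3% |
| Adults | 11 | 0.5 | 0 | 0.1114 | 0.0876 | 0.89 | 8.2% |
| Girls | 22 | 1.0 | 0.4 | 0.0259 | 0.0428 | 1.28 | 1.2% |
| Girls | 22 | 0.5 | 0.5 | 0.0466 | 0.0433 | 0.96 | 5.9% |
| Girls | 22 | 0.5 | 0.3 | 0.0552 | 0.0435 | 0.89 | 8.2% |

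Example, adults at CAC 0.8: T = 0.05 × 0.2 + 0.95/11 = 0.0964; s² = (19 + 0.11 + 0.95)/21 = 0.955; ratio = √(0.0868/0.0964) = 0.95.

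A simulation with a binary outcome at one-third prevalence, for girls at ICC 0.05 (IAC 0.3 to 0.7, CAC 0.5 to 1.0), gave SE ratios from 0.91 to 1.37 and rejection rates from 0.6% to 7.2%. The pattern is the same, and for girls the error is more often conservative.

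**Adult power for 15 points, by estimator.** m = 12 × 0.95 = 11.4, CAC 0.8.
- Variance of a village mean: 0.05 + 0.95/11.4 = 0.1333.
- Correlation of a village's two means: r = 0.05 × 0.8 / 0.1333 = 0.30.
- Mean binomial variance: (0.25 + 0.2275)/2 = 0.23875.
- Endline-only SE: √(2/17 × 0.1333 × 0.23875) = 0.0612.
- Variance factors: interaction 2(1−r) = 1.40; endline only 1; endline adjusted for village baseline 1−r² = 0.91.

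| Estimator | SE | 0.15/SE | Power, Φ(0.15/SE − 1.96) |
|---|---|---|---|
| Time-by-arm interaction | 0.0724 | 2.07 | 54% |
| Endline only | 0.0612 | 2.45 | 69% |
| Endline adjusted for village baseline | 0.0584 | 2.57 | 73% |

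These powers use correct standard errors. In this setting the interaction does worse than ignoring baseline. For girls the loss is smaller: an SE about 4% to 19% larger than with baseline adjustment (linear scale, IAC 0.3 to 0.7, CAC 0.5 to 1.0).

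**The case against.** The strongest reply is that this is one paragraph in a condensed article. It names clusters as random effects but does not rule out a girl-level term or a robust variance, and the full protocol or SAP may give the complete specification. That is fair for details the article does not mention, such as degrees of freedom, and no criticism is made of those. It does not cover a model whose fixed and random parts are written out and applied to two data structures. Nor does it cover two estimators set side by side.

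A second reply is that the baseline sentence only explains what the interaction estimates. That reading is possible, and baseline would then not be used twice. However, the text speaks of adjusting for the dependent variable and does not settle which estimator is meant.

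Parts of the other side stand, and they rule out four stronger readings that a reader might infer.
- **That the primary analysis is faulty.** Child marriage is assessed by a hazard ratio in girls all unmarried at entry, and the wording about relative change is attached to the secondary outcomes.
- **That inference on every secondary outcome is wrong.** The girls' two omissions can nearly cancel, and the adults' error is nominal at CAC 1.
- **That the errors are much larger.** That needs an ICC such as 0.10; the only ICC in the document is 0.05.
- **That precision is certainly lost.** This holds only if the interaction is the estimator used. Both estimators target a valid contrast under randomisation, so the choice between them concerns efficiency.

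**Conclusion.** The point holds for the secondary outcomes only, as a should-fix. Followed as written, the two-wave model generally gives a wrong standard error.
- **Adults:** the error has one direction, anti-conservative whenever CAC is below 1. Type I error is about 6% to 8% at CAC 0.8 to 0.5.
- **Girls:** the direction is not fixed. The SE runs from about 28% too large (CAC 1, IAC 0.4) to about 10% too small (CAC 0.5, IAC 0.3).
- **Power:** if the interaction is used, adult power for 15 points is about 54% rather than 73% at CAC 0.8.

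These sizes rest on assumed CAC and IAC, on the document's ICC of 0.05 carried over to these outcomes, and on a linear approximation to the planned risk-ratio models. The marriage analysis and the 17 clusters per arm are not affected.

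**What to change.** Rewrite the model paragraph in Impact evaluation analysis so that each data structure has one named estimator.
- **Girls' secondary outcomes:** endline value on arm and the girl's own baseline value, with a village random intercept.
- **Adult outcomes:** endline value on arm and the village's baseline proportion or mean of that outcome, with a village random intercept.
- **If the two-wave model is kept:** add a village-by-time random effect and, for girls, a girl random intercept.
- **Child marriage:** state that the time-by-arm model does not apply to it.

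The cost is one paragraph of text. No new data are needed, since both rounds are already part of the design.
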